#### Secondary outcome analyses

• Fatigue, oral and ocular dryness, patient and physician global assessments: For each symptom, a multi-level repeated measures linear regression model will be used to compare VAS scores between groups, models will include the minimisation factors (age, centre, disease duration).

• Salivary and Lacrimal Flow: The flow rates (stimulated salivary flow, unstimulated salivary flow, lacrimal flow) will be compared between the treatment groups using a multi-level repeated measures linear regression model, models will include the values at baseline and the minimisation factors.

• Quality of Life and Disease Activity Indices: The change in each Quality of Life Score, from baseline to 24 and 48 weeks, as measured by SF-36 and each Disease Activity Index (ESSDAI, ESSPRI, SF-36 and PROFAD-SSI) will be compared between treatment groups using a linear regression model, including baseline score values and the minimisation factors.

• Safety and toxicity: Safety analyses will summarise the adverse events (including serious adverse events (SAEs), serious suspected adverse reactions and suspected unexpected serious adverse events), laboratory changes and treatment-related mortality rates. Safety data will be presented by treatment group and relationship to study treatment or underlying PSS. Expected SAEs related to rituximab include infusion-related reactions, infections, cardiovascular events, hepatitis B reactivation and Progressive Multifocal Leukoencephalopathy.

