### Outcomes

The primary outcome is achievement of a 30% reduction at 48 weeks from baseline in either oral dryness or fatigue measured using visual analogue scales (VAS - Range 0-100 mm).

Secondary outcomes at weeks 16, 24, 36 and 48 are: the values of the fatigue and oral dryness scales (VAS), ocular dryness (VAS), patient global assessment of health (VAS), physician global assessments of disease activity and disease damage (0–10 Likert scales), stimulated and unstimulated salivary flow rates, lacrimal flow (Schirmers I test of ocular function), and the EULAR Sjögren’s Syndrome Patient Reported Index (ESSPRI). In addition, further quality of life, and disease damage and disease activity indices at weeks 24 and 48 will be: Medical Outcomes Survey Short Form (SF-36), EQ-5D, EULAR Sjögren’s Syndrome Disease Activity Index (ESSDAI), and the Profile of Fatigue and Discomfort – Sicca Symptoms Inventory (PROFAD-SSI). Outcomes relating to systemic disease activity features at weeks 24 and 48 are: Sjögren’s Syndrome Clinical Activity Index (SCAI), Sjögren’s Syndrome Disease Activity Index (SSDAI), Sjögren’s Syndrome Disease Damage Index (SSDDI), and Sjögren’s Syndrome Damage Index (SSDI). Further outcomes correspond to serological and peripheral blood biomarkers (haematology, biochemistry, serology and immunology assays) measured at each visit. Both patients and physicians complete an exit poll at week 48 asking them if they have suspicions as to which treatment the patient received. Outcomes relating to the optional sub-studies (Glandular histology and composition assessed by biopsy and ultrasound respectively) will be measured at weeks 16 and 48, and the T-Cell sub-study outcomes (peripheral and lesional T cells) will be assessed at week 16 for analysis in this study with samples taken at weeks 24, 36 and 48 for use in future studies.

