#### Primary outcome analyses

A binary logistic regression approach will model the odds of achieving a 30% reduction in symptoms for patients receiving rituximab compared to placebo. Models will include baseline scores for oral dryness and fatigue, as well as disease duration (≤10 years/>10 years), age and centre. The estimated odds ratio for treatment effect will be presented, with the associated 95% confidence interval, and p-value from a likelihood ratio test comparing the models with and without the treatment variable. In addition, the number and proportion of patients in both the rituximab and placebo groups who achieve a reduction in either oral dryness or fatigue >30% between the end of study visit (week 48) and the baseline visit will be summarised. Multiple imputation will be used to impute missing primary endpoint data.

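### The repeated-measures models for fatigue, oral and ocular dryness and the global assessments list no baseline score, unlike the plan's other efficacy models, and so give up precision

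*Protocol article*

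**What the plan says.** Under Secondary outcome analyses, the first bullet of the Protocol article covers fatigue, oral and ocular dryness, and the patient and physician global assessments. For each of these, a repeated-measures model "will be used to compare VAS scores between groups, models will include the minimisation factors (age, centre, disease duration"). No baseline value is named.

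The article's other efficacy models do name it:

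- Salivary and lacrimal flow, second bullet, same type of model: "models will include the values at baseline and the minimisation factors".
- Quality of life and disease activity indices, third bullet: a "linear regression model, including baseline score values and the minimisation factors".
- Primary outcome analyses: "Models will include baseline scores for oral dryness and fatigue".

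The Outcomes section defines the symptom measures as values at follow-up: "Secondary outcomes at weeks 16, 24, 36 and 48 are: the values of the fatigue and oral dryness scales (VAS), ocular dryness (VAS"). They are not changes from baseline, and baseline is not among the listed time points. The Randomisation section names centre, age, disease duration and two consent factors for minimisation. No symptom score is among them.

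**The concern.** A patient's starting score on a symptom scale usually predicts later scores on that scale. If it is left out of the model, the variation between patients that it would explain stays in the standard error of the treatment effect. The multi-level structure does not remove this, because treatment is a comparison between patients. Since minimisation does not balance symptom scores, the arms may also differ at baseline by chance, and an unadjusted model does nothing about such a difference.

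Two of the affected scales, fatigue and oral dryness, are the components of the primary outcome. These models are their continuous analyses, in a trial whose own Discussion calls it small for phase III. An analyst who follows the text literally would adjust flow rates for baseline but not fatigue, and the article gives no reason for the difference.

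**Working it through.** **What the plan's own figures cover.** The article states no SD, correlation or power for these secondary models, so there is no figure to reproduce on this point. The Sample size section gives 50 evaluable patients per group for the binary primary outcome (25% against 55%, two-sided 5%, 80% power). The continuity-corrected two-proportion formula gives 48 per group, which is close to 50. That calculation is unaffected here; only the 50 per arm is carried forward.

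**Inputs**

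- n = 50 per arm and two-sided 5%: Sample size section.
- r, the correlation between baseline and follow-up: not in the document; assumed 0.3 to 0.7.
- True difference of 0.5 SD: assumed.
- SD of 25 mm, used only to express results in millimetres: assumed. It cannot apply to the physician global assessments, which are 0–10 Likert scales.

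**Step 1: single-visit precision.** Adjusting for baseline multiplies the residual variance by 1 − r². The equivalent number per arm is 50/(1 − r²). Power is Φ(0.5 / (√(1 − r²) × √(2/50)) − 1.96). The difference detectable with 80% power is (1.96 + 0.84) × 25 × √(1 − r²) × √(2/50).

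| | Variance factor | Equivalent n per arm | Power for 0.5 SD | Detectable difference, SD 25 mm |
|---|---|---|---|---|
| No baseline | 1.00 | 50 | Φ(2.50 − 1.96) = 70.5% | 14.0 mm |
| r = 0.3 | 0.91 | 55 | Φ(2.62 − 1.96) = 74.6% | 13.4 mm |
| r = 0.5 | 0.75 | 67 | Φ(2.89 − 1.96) = 82.3% | 12.1 mm |
| r = 0.7 | 0.51 | 98 | Φ(3.50 − 1.96) = 93.8% | 10.0 mm |

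**Step 2: mean of the four follow-up visits.** Assume the same correlation r between all visits (compound symmetry). The variance of the four-visit mean, in SD² units, is (1 + 3r)/4 without baseline and (1 + 3r)/4 − r² with it.

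- r = 0.3: 0.385/0.475 = 0.81
- r = 0.5: 0.375/0.625 = 0.60
- r = 0.7: 0.285/0.775 = 0.37

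Under this assumption the relative gain is larger than at a single visit.

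**Step 3: chance imbalance.** The standard error of the baseline difference between arms is √(2/50) = 0.20 SD. An imbalance above 0.20 SD in either direction therefore has probability P(|Z| > 1), about 32%. In an unadjusted model, an imbalance of that size shifts the estimate by r × 0.20 SD: 0.06, 0.10 or 0.14 SD at r = 0.3, 0.5 or 0.7. At SD 25 mm this is 1.5, 2.5 or 3.5 mm out of a 5 mm imbalance.

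**The case against.** The strongest reply is that silence is not exclusion. The bullet says what the models will include, not that nothing else will be. Its bracket names three minimisation factors where the Randomisation section has five, so the list looks abbreviated. The article condenses a fuller protocol, and an analysis plan may complete the covariates. This stands in part: the omission may be a drafting slip. However, the article does state covariates for each model family, and baseline is named in the others. Baseline score is not a minimisation factor either, so shortening that list does not explain its absence.

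A second reply is that a multi-level model can carry baseline as a repeated response with a common mean in both arms, and the concern would then largely disappear. That is a sound method, but nothing in the text describes it, and the listed outcome times start at week 16.

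A third reply concerns size, and it stands. The correlation, SD and difference are all assumptions. Entry requires at least 5/10 for both fatigue and oral dryness, which may narrow the baseline range and lower r. At r = 0.3 the variance reduction is only 9%.

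A reader might also infer that a chance baseline difference passes in full into the treatment estimate, or that the comparison is biased. Neither follows. Only about r of the imbalance carries over, and randomisation keeps the unadjusted estimate unbiased on average. Nor does the document rank these outcomes above the other secondary ones.

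**Conclusion.** The concern holds as a matter of efficiency, not validity. As written, the symptom and global-assessment models are the only ones among the article's efficacy regressions that do not name baseline, and baseline does not enter them by another stated route.

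The loss depends on r. Over the assumed 0.3 to 0.7, leaving baseline out makes the single-visit variance 1.10 to 1.96 times what it would be with adjustment (1/0.91 to 1/0.51). It also leaves the estimate open to partial carry-over of chance imbalance. The direction of the precision effect does not depend on the choice within that range; its size does.

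A reader might infer that the trial's main conclusion is at risk. The text does not support that: the primary model already includes both baseline symptom scores, and the sample size does not rest on these secondary models.

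**What to change.** In the first bullet under Secondary outcome analyses, add the baseline value of the same scale as a covariate in each model, using the form of the flow-rate bullet. If the intention is instead to model baseline as a response with a common mean across arms, state that.

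Fatigue and oral dryness baselines are certainly collected, because the primary endpoint is a percentage reduction from them. For ocular dryness and the patient and physician global assessments, the visible text mentions a baseline visit but does not itemise it. Confirm against the schedule of events, and adjust wherever a baseline value is collected.

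The cost is a few words of text and one parameter per model. The change should be made before unblinding.

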#### Exploratory analyses

Systemic disease activity features: Recently developed measures (SCAI, SSDAI, SSDDI and SSDI) will be summarised for each time-point at which they were measured.

#### Economic evaluation

The primary objective of the economic evaluation is to identify the within study incremental cost effectiveness ratios; the difference in costs between rituximab and placebo divided by the difference in benefits between rituximab and placebo. Analysis will use quality adjusted life years (QALYs) as the summary measurement of benefits. The estimation of QALYs requires the production of utility weights for each health state observed in the trial population. The EQ-5D (Euroqol) instrument will be used for this purpose and estimation of QALYs will use the area under the curve method [17,18]. Secondary analysis will use the SF-36. Resource utilisation will be captured at 16, 24, 36 and 48 weeks after randomisation.

Sensitivity analysis of the incremental cost effectiveness ratio will be undertaken. Bootstrapped incremental costs and benefits will be calculated and used to estimate their joint distribution. These estimates will form a scatterplot on the cost effectiveness plane, and will be used to estimate a 95% cost effectiveness ellipse for the joint distribution of increments costs and benefits, as well as the cost effectiveness acceptability curve for a range of values that a service provider may be willing to pay for one additional QALY. Given the duration of the study discounting is not required.

## Discussion

PSS is characterised by oral and ocular dryness, severe fatigue with reduced quality of life, B-cell hyperactivity, anti-Ro/La antibodies and a 44 times increased risk of B-cell lymphoma. There is no effective systemic therapy that can alter the progress of the disease and no immediate prospect of commercial studies.

This protocol describes a phase III study of 110 patients treated with either rituximab or placebo with re-treatment at 6 months. Although small for a phase III trial it has realistic recruitment and outcome objectives given the prevalence of Sjögren’s syndrome, and it will be the largest trial conducted in the UK to date. Furthermore, the broadly similar patient population and design of the French study by Saraux *et al*. [13] should allow for future meta-analysis of the data.

In parallel with the clinical outcomes of improvement in fatigue and/or dryness the TRACTISS study includes a number of biological outcomes including glandular immunohistochemistry and genetic features, alteration in anti-muscarinic antibody levels, peripheral T-cell numbers and transcriptional profile, and BAFF/BLyS levels. The availability of anti-B-cell therapy for RA means we can also study whether it works in treating the debilitating symptoms of PSS and this is the goal of this study. In addition we will maximise the benefit of the study by also measuring changes in the glands and blood of patients through additional scientific research work that will add support to the clinical findings.

If the results of this study are positive this could lead to anti-B-cell therapy becoming part of routine clinical care for patients with PSS and/or opening new avenues for developing alternative disease-modifying therapeutic approaches for a disease that currently has none available. The incorporated integral scientific components of TRACTISS will maximize the added value of the study to better understand the pathological processes by looking at the effects of rituximab on the glands, blood cells and antibodies in PSS and guide future therapeutic research.

### Trial status

The first patient was enrolled into TRACTISS on the 25th August 2011 and recruitment is due to end December 2013. The study is being conducted in 25 sites across the UK. We expect to report the main trial results in Autumn 2015. Ethical and governance approval for this trial has been obtained from the Leeds West Ethics Committee (ref 10/H1307/99) and the Leeds Teaching Hospitals NHS Trust respectively. The trial progress is monitored by an independent Data Monitoring and Ethics Committee (DMEC) and Trial Steering Committee (TSC).

## Abbreviations

AECG: American-European Consensus Group; Anti-TNF: Anti-tumor necrosis factor; BAFF: B-cell activating factor; BLyS: B Lymphocyte stimulator; CLL: Chronic lymphocytic leukaemia; CTRU: Clinical trials research unit; DMEC: Data monitoring and ethics committee; EQ-5D: European quality of life questionnaire (Five Domain Version); ESSDAI: EULAR Sjögren’s syndrome disease activity index; ESSPRI: EULAR Sjögren’s syndrome patient reported index; EULAR: European league against rheumatism; ITT: Intention to treat; IV: Intra ventricular; LIHS: Leeds institute of health sciences; MTX: Methotrexate; NHL: Non-Hodgkin’s leukaemia; PROFAD-SSI: Profile of fatigue and discomfort – Sicca symptoms inventory; PSS: Primary Sjögren’s syndrome; QALYs: Quality adjusted life years; RA: Rheumatoid arthritis; SAE: Serious adverse event; SCAI: Sjögren’s syndrome clinical activity index; SF-36: Medical outcomes survey short form; SLE: Systemic lupus erythematosus; SSDAI: Sjögren’s syndrome disease activity index; SSDDI: Sjögren’s syndrome damage index; SSDDI: Sjögren’s syndrome disease damage index; TSC: Trial steering committee; UKPSSR: UK primary Sjogren’s syndrome registry; VAS: Visual analogue scale.
